#### Outcome Evaluation and Sample Size Justification

We will compare outcomes achieved by 2 predictive models using the best machine learning algorithm. The first model will use patient, physician profile, and environmental variable features; the second only patient and environmental variable features. We will test 3 hypotheses: adding physician profile features will be associated with reduced (1) costs, (2) hospital admissions, and (3) emergency department visits. We will test each hypothesis twice, once for children and once for adults. Cost data will be log-transformed due to skewed distribution [13]. We will accept the primary hypothesis if the first model can reduce the log cost by 10% multiplied by its standard deviation compared with the second model. One-sided paired-sample *t* test will be used to test the difference in log cost between the 2 models’ outcomes. McNemar’s test will be used to test the difference in hospital admissions and emergency department visits. At a significance level of .05, a sample size of 857 instances has 90% power to confirm the primary hypothesis. The 11th year’s data include approximately 27,000 children and 75,000 adults with asthma, providing adequate power for testing the primary hypothesis.

We will do 2 similar analyses to compare our threshold computation algorithm versus the current method of determining thresholds heuristically (evaluate the technique in Aim 3) and our algorithm for explanations and suggestions versus the current method of giving no explanation and suggestion (evaluate the technique in Aim 2). Physician profile features will be used in either analysis. In the first analysis, we will use the heuristically determined thresholds reported in the literature [15]. In the second analysis, we will use our threshold computation algorithm and estimate outcomes of our algorithm for explanations and suggestions. For an intervention, we will use statistics on its benefits and average cost per patient from the literature [39] where available. If no information is available, the clinician in our research team ([name]) will conservatively estimate these numbers’ minimum and maximum values based on experience. For each number, we will use 5 levels ranging from the minimum to the maximum value. To obtain the entire spectrum of possible outcomes, we will perform sensitivity analysis by varying the level and percentage of suggested interventions that clinicians will use. For the current method of giving no explanation and suggestion, we will proceed in a similar way by letting [name] estimate the lower and upper bounds of the likelihood that clinicians will use an intervention. If [name] has difficulty estimating the likelihood that clinicians will use an intervention, we will interview clinicians using sample patient cases to help with the estimation. Based on its own estimate of the situation, a health care system can check where in the spectrum it will fall.

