## Introduction

### Risk-Stratified Management of Chronic Disease Patients

Chronic diseases affect approximately 52% of Americans and consume 86% of health care costs [1]. Example management strategies for care include case management, disease management, supported self-care, and wellness promotion (listed in Table 1 in descending order of intensity). Each strategy is widely used and has its own benefits and properties [2,3]; for example, most major employers purchase and nearly all private health plans offer case management services [2,4] targeting early interventions at high-risk patients to prevent large expenditures and avoid deterioration of health status. Proper use of case management can reduce hospital admissions and readmissions and emergency department visits by up to 30% to 40% [3,5-9], lower costs by up to 15% [6-10], and improve patient satisfaction, quality of life, and treatment adherence by 30% to 60% [5]. A case management program can cost more than US $5000 per patient per year [6] and typically enrolls only 1% to 3% of targeted patients due to resource limitations [11]. For maximal benefit, only patients expected to incur the highest costs and/or those with the poorest prognoses should be enrolled.

**Table 1 table1:** Description of patient management strategies.

Management strategy	Description
Case management	“A collaborative process that assesses, plans, implements, coordinates, monitors, and evaluates the options and services required to meet [a patient’s] health and human service needs” [12]. It involves a case manager who calls the patient periodically, helps make doctor appointments, and arranges for health and health-related services.
Disease management	Example intervention: check electronic medical records to find and call high-risk patients with the disease who require a specific test, but have not had it for ≥2 years.
Supported self-care	Example intervention: give patients electronic monitoring tools for self-management.
Wellness promotion	Example intervention: mail educational materials on how to maintain health.

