#### Threshold Computation Algorithm

We will conduct quantitative analysis to determine the optimal management level for each risk percentile. We will proceed through the risk percentiles one by one, from the highest to the lowest. Given a risk percentile, we will compute for each management level the average future cost per patient in the percentile if patients in the percentile are put into the level. The level with capacity remaining in its management program and the lowest average future cost per patient will be chosen for the risk percentile.

More specifically, consider a risk percentile and an average patient whose predicted risk falls into the percentile. If the patient is enrolled in a management program, we estimate that the patient’s future cost will change by delta = the program’s cost – the program’s benefit gained by reducing undesirable events=*c*
_
*i*
_–*avg_n*
_
*e*
_**p***c*
_
*e*
_ compared with no enrollment. Here, *c*
_
*i*
_ is the program’s average cost per patient. Factors such as increased medication cost due to better medication adherence are included in *c*
_
*i*
_. *avg_n*
_
*e*
_ is the average number of undesirable events that a patient in the risk percentile will experience in the future. *p* is the percentage of undesirable events the management program can help avoid, reflecting the program’s benefit. *c*
_
*e*
_ is the average cost of experiencing the undesirable event once. *c*
_
*i*
_ and *p* can be obtained from statistics reported in the literature for the management program [39,88]. *avg_n*
_
*e*
_ can be obtained by making predictions on historical data and checking the corresponding statistics for the risk percentile. *c*
_
*e*
_ is obtained from statistics on historical data. The management level with the smallest delta is optimal for the risk percentile. If no statistics on *c*
_
*i*
_ and *p* of a management program are available in the literature, the clinician in our research team ([name]) will provide rough estimates based on experience. We will perform sensitivity analysis when choosing thresholds by varying the estimated values of *c*
_
*i*
_ and *p* to obtain the full spectrum of possible outcomes in Aim 4.

The preceding method performs an exhaustive search among all management levels for each risk percentile. In practice, we would expect *avg_n*
_
*e*

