#### Outcomes

We will focus on the outcomes of costs, hospital admissions, and emergency department visits in the following year. Cost is the primary outcome, reflecting health care use and efficiency of care. Other outcomes are secondary and are indirectly reflected in costs.

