#### Estimate Outcomes

Given a set of attributes and a predictive model, we will estimate each outcome. We will use the same method as in Aim 1 to train the model on the first 10 years’ data. For the 11th year’s data, we will obtain prediction results, compute thresholds for risk strata, then estimate the outcome in a way similar to Aim 3. For example, consider a patient who will have a cost of *h* and experience *n*
_
*e*
_ undesirable events in the following year with no program enrollment. If the patient is enrolled in a management program, we estimate that the patient’s future cost will become *h* + *c*
_
*i*
_–*n*
_
*e*
_**p***c*
_
*e*
_, where *c*
_
*i*
_, *p*, and *c*
_
*e*
_ are as defined in Aim 3. The overall outcome estimate is the aggregate of estimated outcomes for all patients. Using a similar approach, we can identify the minimum accuracy requirement of the model for it to be clinically valuable.

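### McNemar's test for admissions and emergency visits does not fit the expected event counts that the described Aim 4 method produces

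*Protocol article*

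**What the plan says.** All references are to the protocol article.

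- **Test.** Aim 4, Outcome Evaluation and Sample Size Justification, compares two models on the same patients, one with and one without physician profile features. For the two event outcomes, "McNemar’s test will be used to test the difference in hospital admissions and emergency department visits". Each hypothesis is tested in children and again in adults.
- **Outcomes.** Aim 4, Outcomes: "We will focus on the outcomes of costs, hospital admissions, and emergency department visits in the following year". Cost is primary and the others secondary. No per-patient yes/no version of admissions or visits is defined.
- **How outcomes arise.** Aim 4, Estimate Outcomes, says that every outcome will be estimated, and that for the 11th year's data the team will "compute thresholds for risk strata, then estimate the outcome in a way similar to Aim 3". The worked example is for cost: h + c_i − n_e·p·c_e for an enrolled patient. Then: "The overall outcome estimate is the aggregate of estimated outcomes for all patients".
- **Meaning of p.** Aim 3, Threshold Computation Algorithm: p "is the percentage of undesirable events the management program can help avoid, reflecting the program’s benefit". It is an average fraction that multiplies a number of events.
- **Size of p.** The Introduction (Risk-Stratified Management of Chronic Disease Patients) says that case management can "reduce hospital admissions and readmissions and emergency department visits by up to 30% to 40" per cent.

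**The concern.** McNemar's test draws all its information from discordant pairs: patients with the event under one model and without it under the other. The described method does not switch events on or off for individuals. It scales each enrolled patient's count down by a fraction. A programme that removes part of everyone's expected events moves nobody from some events to none, so the test sees no change however large the simulated reduction.

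Two of the three Aim 4 hypotheses rest on this test, each in two populations, which makes four tests. The same section announces two further comparisons run in a similar way, for the threshold algorithm and for the explanation algorithm. If those reuse the test, they inherit the problem.

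**Working it through.** **1. The section's own figure.** No sample size is given for the McNemar tests. The one figure given is for log cost: effect 0.1 SD, one-sided .05, 90% power.

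n = ((1.645 + 1.282)/0.1)² ≈ 856.4, rounded up to 857.

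This matches the stated 857. (The exact t calculation gives 858; power at 857 is 0.8998.) Nothing below changes it.

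**2. The method applied to events.** For a patient with n_e events without enrolment, the expected count under model m is

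y_m = n_e(1 − p_m),

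where p_m belongs to the management level that model m assigns, and p_m = 0 if the patient is not enrolled.

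| n_e | not enrolled | p = 0.30 | p = 0.40 |
|---|---|---|---|
| 0 | 0 | 0 | 0 |
| 1 | 1 | 0.7 | 0.6 |
| 2 | 2 | 1.4 | 1.2 |
| 3 | 3 | 2.1 | 1.8 |

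**3. Any-event status.** If p_m < 1, then y_m > 0 exactly when n_e > 0. The right-hand condition does not involve the model, so status is the same under both models for every patient. The discordant counts are b = c = 0, and (b − c)²/(b + c) = 0/0. This needs only p < 1. It does not depend on the cohort, the event rate or the accuracy of either model.

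**4. What other rules would do.** The article states none of the rules below. To see how much the choice matters, take an assumed cohort: 27,000 patients, 1,846 of them with at least one event, 1% to 10% enrolled, p = 0.30 or 0.40, and the first model ranking risk better than the second. Entries are patients with the event under the first model only / under the second model only. They are the same at both values of p.

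| Enrolled | count > 0 | nearest integer ≥ 1 | count ≥ 1 |
|---|---|---|---|
| 1% | 0/0 | 0/0 | 48/59 |
| 3% | 0/0 | 0/0 | 110/166 |
| 10% | 0/0 | 0/0 | 258/342 |

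- *Cut at ≥ 1.* At 3% enrolled, (110 − 166)²/(110 + 166) = 3136/276 = 11.4, where the > 0 rule gives 0/0 on the same data. From the table in step 2, the cut counts an enrolled one-event patient (0.6 or 0.7 expected events) as fully prevented and an enrolled two-event patient (1.2 or 1.4) as not helped at all. The result is therefore the same for p = 0.30 and p = 0.40.
- *Random removal of individual events.* Mean discordant pairs run from about 16/21 (1% enrolled, p = 0.30) to 152/193 (10% enrolled, p = 0.40). At 3% enrolled and p = 0.40, the p-value from a single draw has a 5th to 95th percentile range of 0.001 to 0.42, and 55% of draws fall below .05. Draws were made independently for the two models.
- *Any yes/no rule* ignores repeat events, although p is defined on numbers of events.

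**The case against.** The strongest reply is that the article nowhere writes n_e(1 − p) for admissions or visits. Its per-patient formula is an example, and the example is cost. Aim 4 is titled as a simulation, and a condensed article may leave an event-drawing rule and a binary definition to the full plan. Under such a rule discordant pairs would exist, as step 4 shows.

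Part of this stands. The extension to events is an inference. It rests on the statement that every outcome will be estimated and on "then estimate the outcome in a way similar to Aim 3". It is, however, the only method given, and the described steps contain no random draw, rounding rule or dichotomy. The article also did not leave the test open: it named one, and that test does not match the quantity its method yields. This is a conflict between two stated choices and not a missing detail.

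A reader might go further and infer that McNemar's test can never be used here, or that Aim 4 as a whole fails. The documents support neither. The 0/0 result belongs to the deterministic reading. Simulated admissions and visits can still be summed and compared. Both outcomes are secondary to cost.

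**Conclusion.** The mismatch is real but limited. If the described method is applied to events deterministically, and any event is the binary outcome, the four secondary tests have no discordant pairs and yield no result at any sample size. The only assumptions are that reading and p < 1, which the article's own 30% to 40% supports for case management. Under the alternatives the test is computable, but its answer depends on an unstated cut or a random draw. The step 4 counts rest on an assumed cohort and show sensitivity only; the conclusion comes from the algebra. The primary log-cost test and its 857 are not touched by this point.

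**What to change.** **Preferred.** Replace McNemar's test for these two outcomes with the paired per-patient difference in expected events between the models. Use n_e(1 − p_level), with the p of the management level that each model assigns, and n_e where the patient is not enrolled. A single p will not do, because p is specific to the programme and Aim 4 uses a hierarchy of levels. Give a bootstrap 95% interval that resamples patients. Take the hypothesis as supported if the interval excludes zero in favour of the model with physician profile features. Report events avoided per 1,000 patients across the range of p already planned for the sensitivity analysis, since the interval does not carry uncertainty in p.

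**Alternative.** Keep McNemar's test, but only with a pre-specified per-patient binary outcome and an event-level random simulation summarised over many repeated draws. Repeat events would still be lost.

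**Cost.** A short change of wording and slightly more analysis work. No new data are needed, and the primary analysis and its sample size stay as they are.

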### Aim 2: Develop an Algorithm to Explain Prediction Results and Suggest Tailored Interventions

For patients with predicted risk greater than a predetermined threshold, such as the 95th percentile, this aim will explain prediction results and suggest tailored interventions. These explanations and suggestions can help clinicians make final decisions on the management levels and interventions for these patients.

Prediction accuracy and model interpretability are frequently 2 conflicting goals. A model achieving high accuracy is usually complex and difficult to interpret. How to achieve both goals simultaneously has been a long-standing open problem. Our key idea to solve this problem is to separate prediction and explanation by using 2 models concurrently, each for a different purpose. The first model makes predictions and targets maximizing accuracy. In this study, this model is the best one built for the outcome variable in Aim 1. The second model is rule-based and easy to interpret. It is used to explain the first model’s results rather than make predictions. The rules used in the second model are mined directly from historical data rather than coming from the first model. For each patient whom the first model predicts to be at high risk, the second model will show zero or more rules. Each rule gives a reason why the patient is predicted to be at high risk. Because some patients can be at high risk for rare reasons that are difficult to identify, we make no attempt to ensure that at least one rule will be shown for every patient predicted to be at high risk. Instead, we focus on common reasons that are more important and relevant to the patient population than rare ones. We expect most high-risk patients to be covered by one or more common reasons.

We will use an associative classifier [83-85] from the data mining field as the second model. Associative classifiers can handle both numerical and categorical variables and be built efficiently from historical data. Compared with several other rule-based models, an associative classifier includes a more complete set of interesting and useful rules and can better explain prediction results. For ease of description, our presentation focuses on the case that each patient has exactly one data instance (row). The case in which a patient has more than one data instance can be handled similarly. We will proceed in 3 steps.

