#### Performance Evaluation

The algorithm for explanations and suggestions will be evaluated in Aim 4.

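### The Aim 4 comparison of the explanation-and-suggestion algorithm with no suggestion runs on assumed uptake and benefit, so it cannot show that the tailoring works and should be reported as a scenario projection without a test

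*Protocol article*

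**What the plan says.** Aim 2, Performance Evaluation, defers the matter: "The algorithm for explanations and suggestions will be evaluated in Aim 4". Aim 4, Outcome Evaluation and Sample Size Justification, then announces two analyses similar to the one for physician profile features. The second sets the algorithm against current practice without explanations or suggestions, and in it "we will use our threshold computation algorithm and estimate outcomes of our algorithm for explanations and suggestions".

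The inputs to that second analysis are:

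- **Benefit and cost of an intervention:** "we will use statistics on its benefits and average cost per patient from the literature [39] where available". Otherwise a clinician on the research team "will conservatively estimate these numbers’ minimum and maximum values based on experience", with five levels per number.
- **Uptake with the algorithm:** "we will perform sensitivity analysis by varying the level and percentage of suggested interventions that clinicians will use".
- **Uptake without it:** lower and upper bounds estimated by the same clinician, with interviews of clinicians on sample cases as a fallback.

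The model being evaluated is separate from the predictive model: "The rules used in the second model are mined directly from historical data rather than coming from the first model". The only other success rule for Aim 2 is coverage: a nontrivial share of high-risk patients, for example at least 20%, should fall under actionable rules.

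**The concern.** The Introduction argues that an intervention aimed at the patient's own reason for risk tends to work better than a nonspecific one. An evaluation of the algorithm should therefore be able to come out badly if the rules pick the wrong reasons. As described, the Aim 4 comparison cannot do that. It sets more use of interventions assumed to be effective against less use of them, and a mismatched suggestion earns the same credit as a fitting one.

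The coverage criterion does not fill the gap, because it counts patients who have an actionable rule and not rules that are right. At stake is what may be concluded about Aim 2. A favourable result, especially one with a p value from many thousands of patients, could be read as evidence for tailoring when it only restates the inputs.

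**Working it through.** **1. The plan's own figure.** The similar analysis for physician profile features uses a one-sided paired t test at .05 with an effect of 0.1 SD of log cost. By the normal formula, n = ((1.645 + 1.282)/0.1)² ≈ 856.4, rounded up to 857. The stated 857 reproduces and is not in dispute.

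**2. Formula.** Aim 4, Estimate Outcomes, gives the cost of an enrolled patient as h + c_i − n_e·p·c_e. Aim 3 defines p as the share of events that the program helps avoid, which is a property of the program and not of its fit to the patient. The article gives no formula for a single intervention. Extending this one to intervention j used with probability u gives

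estimated cost = h + u·(c_j − b_j·n_e·c_e).

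With u1 for uptake with suggestions and u0 without, h cancels and

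difference = (u1 − u0)·(c_j − b_j·n_e·c_e).

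Only n_e and c_e come from the data set, and they are the same in both arms.

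**3. Sign and break-even.** Assumed for illustration, not in the article: c_e = $2,000 and n_e = 1.

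| u1, u0 | b | c | Difference per patient |
|---|---|---|---|
| 0.2, 0.2 | any | any | 0 |
| 0.5, 0.3 | 0.30 | $80 | 0.2 × (80 − 600) = −$104 |
| 0.5, 0.3 | 0.15 | $80 | 0.2 × (80 − 300) = −$44 |
| 0.5, 0.3 | 0.05 | $150 | 0.2 × (150 − 100) = +$10 |
| 0.8, 0.1 | 0.30 | $80 | 0.7 × (80 − 600) = −$364 |
| 0.3, 0.5 | 0.30 | $80 | −0.2 × (80 − 600) = +$104 |

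The sign changes at u1 = u0, and at b = c/(n_e·c_e). The latter is 80/2,000 = 4% for an $80 intervention and 150/2,000 = 7.5% for a $150 one. Both break-even points lie entirely in the assumptions.

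**4. Shuffling suggestions.** The simulation flags 1,350 children (5% of 27,000). It uses five intervention types with b from 0.05 to 0.30 and c from $20 to $150, c_e = $2,000 and uptake 0.5 versus 0.3. Suggestions are permuted among flagged patients only, with the comparator arm held fixed. Total score:

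| Setting | Own suggestions | Shuffled |
|---|---|---|
| Equal b and c for all types | −$53,880 | −$53,880 |
| Type unrelated to n_e (mean of 60 data sets) | −$61,551 | −$60,485 |
| Costlier, more effective types go to patients with more events | −$74,280 | −$42,111 |
| The reverse | −$45,900 | −$79,668 |

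In the second row the ratio is 0.98, which is simulation noise. In the last two rows the gap comes from the covariance of b_j with n_e. No row contains a term for whether the suggestion is right.

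**5. The planned scale.** Different assumptions here: mean 0.6 events, c_e = $2,000, mean b = 0.20, c = $50, uptake 0.5 versus 0.2. The mean saving is 0.3 × (0.20 × 0.6 × 2,000 − 50) = $57. Baseline cost is taken as lognormal (median $2,000 or $5,000, log SD 1.0 or 1.3) plus $2,000 per event, with 200 runs each. The one-sided paired t test on log cost rejects in 100% of runs, for own and for shuffled suggestions alike, in three of the four baselines. In the fourth it rejects in 68% and 69%. The fall is 0.002 to 0.006 SD of log cost, or 0.06 to 0.31 SD of the paired difference. With b = 0.10 and c = $200 the mean is a loss, 0.3 × (120 − 200) = −$24, and the test rejects in 0% of runs either way.

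**The case against.** The strongest reply is that the article already presents this as simulation. It promises a full range of outcomes, lets each health care system find its own place in that range, and leaves real impact to a later randomized trial. This stands in part, and it makes the repair mostly one of reporting. But the same section names the comparison as the evaluation of the Aim 2 technique and ties it to an analysis that ends in a test. Every input that is varied is one of the same assumptions, so no point in the range can count against the rules.

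A second reply is that the rules do meet data and judgement: minimum support and confidence, and clinicians who remove implausible rules. That is true, but these act before the scoring and do not enter it. The article also allows the thresholds to be lowered to obtain enough rules.

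A third reply limits the claim, and it stands. A reader might infer that shuffled suggestions always score as well as the algorithm's own. They do so exactly when benefit and cost are equal across interventions, and in expectation when type is unrelated to event count. Otherwise they can score better or worse. A shuffle also produces suggestions that the algorithm could not make, since a rule is shown only to patients who satisfy it.

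A reader might also infer that the plan is bound to declare a cost reduction. The documents do not support that. Unfavourable assumed inputs give a loss. If the 10% rule refers to the SD of log cost, the falls in step 5 are far below 0.1 SD. If it refers to the SD of the paired difference, the result is mixed. That the test carries over at all rests on the word for similar analyses and not on an explicit statement.

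**Conclusion.** The concern holds in a limited form. The comparison is driven by assumed uptake and by assumed benefit and cost, applied to the same event counts in both arms. It can project what happens if clinicians use more interventions of a given assumed value. It cannot show that the algorithm matches interventions to reasons for risk, and a test modelled on the one for physician profile features would be uninformative about the rules whatever the sample size.

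The size of the projected effect is whatever the inputs make it: zero at equal uptake, and in the illustrations from −$364 to +$104 per patient. These dollar figures rest on assumed event costs, benefits and uptakes. The structural point rests only on extending the article's program formula to single interventions. It does not need shuffled and own suggestions to score equally, nor a particular test result.

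**What to change.** In Aim 4, Outcome Evaluation and Sample Size Justification:

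1. Report the comparison with no suggestion only as a scenario projection. Give the break-even uptake difference and the break-even net benefit, with no p value and no accept-or-reject rule.
2. Base any statement about the rules on observed data already held. Mine the rules on the first 10 years. Report each rule's confidence and lift in the 11th-year data against the base rate in all asthma patients.
3. State that step 2 tests association with high risk and not the benefit of an intervention.

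Do not try to repair the score by scaling an intervention's benefit by the excess event rate of rule-matching patients among those flagged. Excess risk is not intervention benefit, and flagged patients were selected on a risk score built from the same features. A shuffled control arm scored with the present formula would add nothing either.

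The cost is a small amount of extra analysis on data in hand, a change of wording, and a weaker claim for Aim 2.
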